# Effects of 12-month home-based physiotherapy on duration of living at home and functional capacity among older persons with signs of frailty or with a recent hip fracture - protocol of a randomized controlled trial (HIPFRA study)

**DOI:** 10.1186/s12877-018-0916-y

**Published:** 2018-10-01

**Keywords:** Frail elderly, Hip fractures, Community-dwelling, Home-based physiotherapy, Duration of living at home, Functional capacity, Social and health care services

## Abstract

**Background:**

Health concerns, such as frailty and osteoporotic fractures decrease functional capacity and increase use of health and social care services in the aging population. The ability to continue living at home is dependent on functional capacity, which can be enhanced by rehabilitation.

We study the effects of a 12-month home-based physiotherapy program with 12-month follow-up on duration of living at home, functional capacity, and the use of social and health care services among older persons with signs of frailty, or with a recently operated hip fracture.

**Methods:**

This is a non-blinded, parallel group, randomized controlled trial performed in South Karelia Social and Health Care District, Finland (population 131,000). Three hundred community-dwelling older persons with signs of frailty (age ≥ 65) and 300 persons with a recent hip fracture (age ≥ 60) will be recruited. Frailty is screened by FRAIL questionnaire and verified by modified Fried’s frailty criteria. Both patient groups will be randomized separately to a physiotherapy and a usual care arm. Individualized, structured and progressive physiotherapy will be carried out for 60 min, twice a week for 12 months at the participant’s home. The primary outcome at 24 months is duration of living at home. Our hypothesis is that persons assigned to the physiotherapy arm will live at home for six months longer than those in the usual care arm. Secondary outcomes are functional capacity, frailty status, health-related quality-of-life, falls, use and costs of social and health care services, and mortality. Assessments, among others Short Physical Performance Battery, Functional Independence Measure, Mini Nutritional Assessment, and Mini-Mental State Examination will be performed at the participant’s home at baseline, 3, 6, and 12 months. Register data on the use and costs of social and health care services, and mortality will be monitored for 24 months.

**Discussion:**

Our trial will provide new knowledge on the potential of intensive, long-term home-based physiotherapy among older persons at risk for disabilities, to enhance functional capacity and thereby to postpone the need for institutional care, and diminish the use of social and health care services.

**Trial registration:**

ClinicalTrials.gov Identifier: NCT02305433, Registered Nov 28, 2014.

## Background

In the aging population, one of the major burdens in social and health care is frailty. Frailty is a multidimensional condition, related to poor resolution of homeostasis after stressor events [1–3]. It can lead to increased vulnerability, disability, risk of falling, need for long-term care, mortality [1–3], and is associated with increased health care costs [4]. Hip fractures are another major burden causing morbidity, impairments, increased need for care, and mortality [5–7]. The yearly economic burden of hip fractures in Europe alone is estimated to be over 16 billion euros [7].

In persons over 65 years the prevalence of frailty varies depending on the criteria used, being from 4 to 59% [8, 9]. The most common definition is based on the frailty phenotype [1], which includes five criteria: unintentional weight loss, exhaustion, physical inactivity, slow walking speed, and weak grip strength. The prevalence of frailty increases with age and is higher among women than among men [10]. Both frailty and pre-frailty states are significant predictors of nursing home placement [11].

Worldwide the incidence of hip fractures varies widely and is highest in North Western Europe [12]. In western countries 10–20% of the persons are institutionalized when evaluated 6–12 months after the hip fracture [13], and 11% change their dwelling (from home to institution or vice versa) during 4–12 months after the fracture [14]. At one year since the fracture 42% of the patients have not recovered to their pre-fracture mobility level, and 29% do not achieve the same level of activities of daily living that they had before the fracture [15]. Excess mortality during the first post-fracture year of hip fracture patients is 8–36% [16]. Frailty is common among hip fracture patients [17], and the frailty status influences the recovery [18].

Physical activity has beneficial effects on muscle strength and endurance in older adults [19]. Frailty is an indication to start physical exercise [19] to improve functional capacity [20]. Multicomponent exercise interventions (including aerobic, strength, balance and flexibility exercises) reduce the incidence, prevalence and severity of frailty [21, 22], and enhance functional capacity [18, 23] and overall mobility [24] of hip fracture patients.

To our knowledge, long-term home-based physiotherapy and whether it can prolong duration of living at home have not been studied extensively in community-dwelling older persons with signs of frailty or with a recently operated hip fracture. Our objective is to study the effects of a structured 12-month home-based physiotherapy program with 12-month follow-up on duration of living at home, functional capacity, and the use of social and health care services. The main hypothesis is that home-based physiotherapy lengthens the duration of living at home by six months as compared to usual care in both patient groups. We also hypothesize that physiotherapy improves functional capacity, and decreases the use and costs of social and health care services.

## Methods

### Design

HIPFRA study is a parallel group, non-blinded, randomized controlled trial carried out in Finland, in South Karelia Social and Health Care District (Eksote), population 131,000, of whom 25% were 65 years or older in 2015. The study lasts for 24 months and has two phases; 1) home-based physiotherapy intervention for the first 12 months, and 2) registry follow-up for the second 12 months. The study has started in December 2014 and the final follow-up period ends in December 2019. For a more detailed timetable, see Fig. 1.

**Fig. 1 Fig1:**
[figure not shown]
Timetable

### Outcomes of the study

The primary outcome is duration of living at home. The secondary outcomes are functional capacity, frailty status, health-related quality-of-life, and number of falls, use and costs of social and health care services, and mortality.

### Participants and eligibility criteria

The target population is older adults with signs of frailty or with a recently operated hip fracture, who live at home, are able to walk indoors without or with mobility aids, and are able to communicate in Finnish.

For persons with signs of frailty the inclusion criteria are: 1) one or more points from FRAIL questionnaire [25] (screening), 2) one or more points from modified Fried et al.’s frailty criteria [1] (verification), 3) age 65 or older, and 4) Mini-Mental State Examination (MMSE) [26] score ≥ 17. For hip fracture patients the inclusion criteria are 1) ICD-10 diagnosis codes S72.0, S72.1, S72.2, 2) the index fracture is the first operated one in the present hip, 3) age 60 or older, and 4) Mini-Mental State Examination (MMSE) [26] score ≥ 12.

Exclusion criteria for both patient groups are: 1) resident in institutional care, 2) advanced diseases which prevent from participating in long-term physiotherapy, such as severe neurological diseases (e.g. multiple sclerosis, cerebrovascular disorders), cardiovascular diseases with severely impaired physical capacity (NYHA class III or IV), severe musculoskeletal diseases (e.g. severe rheumatoid arthritis), or severe or acute mental problems (major depression, psychosis or schizophrenia), 3) alcohol or drug abuse, 4) severe problems with hearing or eyesight, or 5) terminal illnesses.

### Randomization

A computer-generated random allocation sequence was prepared by a statistician at University of Helsinki. The statistician is not involved in the management of patients. The two patient groups are randomized separately to a home-based physiotherapy and a usual care arm. Random allocation is performed by the project manager using the computer program, in consecutive order after baseline assessments. The randomization block size varies from 2 to 10 and the sequence is concealed. The project manager informs the participant by telephone about the allocation result. If the participant is allocated to the physiotherapy arm, the manager also informs the physiotherapist by telephone about the new rehabilitee, and physiotherapy starts within a week.

### Recruitment

#### Recruitment of persons with signs of frailty

Potential participants are informed about the study by advertisements in local newspapers or by Eksote personnel. The recruitment process has two phases (Fig. 2). First, frailty screening is carried out using FRAIL questionnaire [25] either in face-to-face contacts or over the phone by Eksote personnel. In the second phase, the study nurse visits the person’s home, gives oral and written information about the study, checks that all the inclusion criteria and none of the exclusion criteria are fulfilled, and verifies the frailty status using modified Fried’s criteria [1]. The criteria were modified by assessing physical activity using the question on frequency of physical activity according to Health Behaviour and Health of the Finnish Elderly survey [27], and by using a cut-off value of 8.7 s for the 4-m walking time, which is based on the lowest quarter for persons aged 71 and older in Short Physical Performance Battery [28].

**Fig. 2 Fig2:**
[figure not shown]
Flow chart

#### Recruitment of persons with a recent hip fracture

Recruitment begins at Eksote Rehabilitation Inpatient Center, to which the majority of the hip fracture patients are transferred from Eksote orthopedic wards in less than a week after surgery. The study nurse meets possibly eligible patients in the rehabilitation inpatient center and gives them oral and written information about the study. For those who are interested in participating, a home visit is performed by the nurse within a week after discharge. The content of the home visit is the same as for the persons with signs of frailty.

### Assessments

Previously validated methods for data collection are used in HIPFRA study. Information about the main outcome, duration of living at home, is retrieved from the electronic health records (EHR) of Eksote. The duration of living at home is defined as number of days lived at home during 24 months. Days spent in hospital or in institutional care reduces the number of days lived at home. Change to reside permanently in institutional care or death (within 24 months) are defined as end points.

Interviews, questionnaires, measurements and register information are used to collect data for secondary outcomes. Measurements and interviews based on structured questionnaires are performed at baseline, and after 3, 6, and 12 months at the participant’s home by the study physiotherapist or the study nurse, who are not blinded to randomization. The visit lasts approximately for one and half hours. Before the baseline assessment the participant signs a written informed consent. Before visits the participants are mailed self-reported questionnaires. Register information (for 0–24 months) on the use and costs of social and health care services, medication and mortality will be retrieved from Eksote EHR, the Population Register Centre, and the registers of the Social Insurance Institution (for 0–24 months). Assessment methods of outcomes and other parameters, and the assessment schedule during 24 months are presented in Table 1.

**Table 1 Tab1:** Outcomes, assessment methods and schedule

Outcomes	Parameters and measures [reference]	Scale	Assessment method	Assessment time points (months from the beginning)				
				0	3	6	12	24
Primary outcome	Duration of living at home (days) during 24 months	1–730	Register information					x
Secondary outcomes								
Functional capacity	Instrumental Activities of Daily Living (IADL) [54]	8-31	Interview based on a structured questionnaire	x	x	x	x	
	Functional Independence Measure (FIM) [55]	18–126	Interview based on a structured questionnaire	x	x	x	x	
	Short Physical Performance Battery (SPPB) [28, 56]	0–12	Measurement	x	x	x	x	
	Grip strength (Saehan dynamometer, model Sh5001, South Korea) [57]		Measurement	x	x	x	x	
Frailty status	Fried et al.’s frailty criteria (modified) [1]	0–5	Interview based on a structured questionnaire and measurement	x			x	
Quality-of-life	Health-related quality-of-life (HRQoL) (15D©) [58, 59]	15–75	Self-reported questionnaire	x	x	x	x	
Falls	Number of falls		Interview based on a structured questionnaire	x	x	x	x	
Service use and costs	Use and costs of social and health care services, and medication		Register data (0–12 months and 13–24 months) from EHR and Social Insurance Institution				x	x
Mortality	Mortality		Register data from EHR					x
Other outcomes								
Cognition	Mini-Mental State Examination (MMSE) [26]	0–30	Interview based on a structured questionnaire	x		x	x	
Depressive symptoms	Geriatric Depression Scale (GDS-15) [60]	0–15	Interview based on a structured questionnaire	x	x	x	x	
Nutritional status	Mini Nutritional Assessment (MNA) [38]	0–30	Interview based on a structured questionnaire	x	x	x	x	
Fear of falling	Falls Efficacy Scale International (FES-I) [61, 62]	16–64	Interview based on a structured questionnaire	x	x	x	x	
Social support	Social Provision Scale (SPS) [63]	24–96	Self-reported questionnaire	x		x	x	
Health status	Weight (Omron HN289, Japan)		Measurement	x	x	x	x	
	Height (KaWe PERSON-CHECK, Germany)		Measurement	x	x	x	x	
	BMI		Calculated from weight and height	x	x	x	x	
	Diseases diagnosed by a physician		Interview based on a structured questionnaire and EHR	x			x	
	Medication		Interview based on a structured questionnaire and EHR	x	x	x	x	
	Pain (Visual Analogue Scale, VAS) [64]	0–100	Interview based on a structured questionnaire	x	x	x	x	
	Medical and mobility aids		Interview based on a structured questionnaire and EHR	x	x	x	x	
	Perceived health [27]		Interview based on a structured questionnaire	x	x	x	x	
	Perceived mobility and physical fitness [27]		Interview based on a structured questionnaire	x	x	x	x	
	Hip fracture surgery (details of operation, inpatient rehabilitation)		EHR	x				
Home services	Home care and home health care		Interview based on a structured questionnaire and EHR	x	x	x	x	
	Home renovations		Interview based on a structured questionnaire and EHR	x	x	x	x	
Lifestyle	Physical activity [27]		Interview based on a structured questionnaire	x	x	x	x	
	Alcohol consumption (AUDIT-C) [65]	0–12	Interview based on a structured questionnaire	x	x	x	x	
	Smoking [27]		Interview based on a structured questionnaire	x	x	x	x	
Background information	Demographic factors (age, marital, status, education, previous occupation)		Interview based on a structured questionnaire	x				
	Type of dwelling and household		Interview based on a structured questionnaire	x	x	x	x	

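### Service use and costs have no costed pre-randomisation total, so the cost comparison is valid but less precise than a wider register request could make it

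*Protocol article*

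**What the plan says.** The Assessments section of the protocol article sets the register period in the text: "Register information (for 0–24 months) on the use and costs of social and health care services, medication and mortality will be retrieved from Eksote EHR" and from two other national sources. The sentence gives the 0 to 24 month period twice. Table 1 repeats it for service use and costs, split by year: "Register data (0–12 months and 13–24 months) from EHR and Social Insurance Institution". That row is marked at months 12 and 24 and not at month 0.

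The outcome carries a hypothesis. The Background expects that physiotherapy "decreases the use and costs of social and health care services". The Statistical analyses section plans a log-link gamma model for service use and costs and names no prior-use covariate.

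Table 1 does record some service items at month 0, under other outcomes. "Home care and home health care", home renovations, medication, and medical and mobility aids are all taken at month 0, with the method given as "Interview based on a structured questionnaire and EHR". Diagnosed diseases are recorded then too. For hip fracture patients, "Hip fracture surgery (details of operation, inpatient rehabilitation") is read from the EHR at month 0.

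**The concern.** Among the secondary outcomes in Table 1, the functional measures, grip strength, frailty status, quality of life and falls all have a month-0 value. Only service use and costs, and mortality, do not. Mortality cannot have a baseline, so service use and costs is the one secondary outcome that could have one and lacks it.

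The gap lies in data collection, not only in analysis. If the earlier months are never requested, no later analysis plan can adjust for them. Costs are usually skewed, which the choice of a gamma model acknowledges. If past users tend to be future users, prior use would explain part of that spread. At stake is the width of the interval around the cost difference. Prior hospital days could also serve as a covariate for days lived at home, because hospital days are subtracted from that outcome.

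**Working it through.** **What is and is not available before randomisation**

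| Item | Month 0 in Table 1 |
|---|---|
| Home care, home renovations, medication, aids | yes, interview and EHR |
| Diagnosed diseases | yes, interview and EHR |
| Hip operation and inpatient rehabilitation | yes, EHR |
| Function, frailty, cognition | yes, interview or measurement |
| Prior hospital (beyond the hip fracture stay), institutional and outpatient use | not listed |
| Any costed total of prior use | not listed |

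The operation and the inpatient rehabilitation come before the nurse's home visit, and allocation is made "in consecutive order after baseline assessments". The EHR is therefore already read for events before randomisation. For the Social Insurance Institution registers, the article shows nothing comparable.

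**Precision gain from a prior-cost covariate**

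The article gives no sample size, standard deviation or correlation for costs, so there is no figure of its own to reproduce. Inputs:

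- Participants: 300 per patient group (Statistical analyses); 150 per arm if allocation is 1:1, which is assumed. Losses are ignored.
- Alpha 0.05, taken as two-sided, and power 0.80, as for the primary outcome.
- Correlation ρ between prior and follow-up cost: assumed, shown as a range.

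Formulas (linear-model approximation):

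- residual variance factor = 1 − ρ²
- confidence interval width factor = √(1 − ρ²)
- equivalent size per arm = 150 / (1 − ρ²)
- smallest detectable difference in SD units = (1.960 + 0.842) × √(2/150) × √(1 − ρ²) = 0.323 × √(1 − ρ²)

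| ρ (assumed) | Variance factor | CI width factor | Equivalent n per arm | Detectable difference (SD) |
|---|---|---|---|---|
| 0 | 1.00 | 1.000 | 150 | 0.323 |
| 0.1 | 0.99 | 0.995 | 152 | 0.322 |
| 0.2 | 0.96 | 0.980 | 156 | 0.317 |
| 0.3 | 0.91 | 0.954 | 165 | 0.309 |
| 0.5 | 0.75 | 0.866 | 200 | 0.280 |

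At ρ from 0.3 to 0.5 the interval narrows by 5 to 13%, because 1 − 0.954 = 0.046 and 1 − 0.866 = 0.134. At ρ from 0.1 to 0.2 it narrows by 0.5 to 2%.

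**The same on the cost-ratio scale**

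With a log link, take the standard error of the log ratio as roughly CV × √(2/150), where the coefficient of variation (CV) is also assumed. At CV 1.5, the detectable ratio is exp(−2.802 × 1.5 × 0.1155 × √(1 − ρ²)). This gives 0.616 at ρ = 0, 0.629 at ρ = 0.3 and 0.657 at ρ = 0.5. The smallest detectable saving moves from about 38% to 37% and 34%.

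**The case against.** The strongest reply is that nothing here is wrong. The window is stated consistently, matches the 24-month study period, and describes when the outcome is counted. It does not say that earlier records are excluded, and a journal article may leave covariates to a fuller plan. Much of this stands: there is no contradiction and no bias. But the article states the register request with its limits in both text and table. A covariate from months outside that request cannot be added at the analysis stage.

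A second reply is that the gain is overstated. The correlation is assumed, and the formula belongs to a linear model, not a log-link gamma model. It also compares adjustment with no adjustment at all, whereas the useful gain is the increment over the month-0 items already held. In the hip fracture group, follow-up use comes after a new acute event, so prior use may predict it less well. Residents of institutional care are excluded, which restricts the range of prior institutional days. All of this stands and makes the size uncertain.

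A third reply concerns feasibility. The study began in December 2014 and the last 24-month follow-up ends in December 2019, so enrolment was due to end by about December 2017, before the article appeared in October 2018. Consent was signed before baseline. New consent wording could not reach these participants, and the article does not state the scope of permits or consent.

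Three stronger readings are tempting, and the document does not support them:

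- That there is no baseline for service use at all. Home care, medication, aids and home renovations are recorded at month 0.
- That an imbalance in heavy users could be neither seen nor adjusted for. Diagnoses, medication, home care and function are plausible proxies, and baseline comparisons between arms are planned.
- That the cost comparison is biased. Randomisation protects it.

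**Conclusion.** The point holds as a missed gain in precision. No costed pre-randomisation total is listed, nor is prior hospital, institutional and outpatient use, and the register window is fixed so that neither would be collected. The unadjusted randomised comparison of costs remains valid.

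The likely benefit is modest. It is about 5 to 13% off the interval width if the correlation is 0.3 to 0.5, and 2% or less if it is 0.1 to 0.2. These figures rest on an assumed correlation, 150 per arm, a linear approximation and no other baseline covariates. It would be wrong to read the equivalent sample gain (165/150 − 1 = 10% to 200/150 − 1 = 33%) as an established figure. It would also be wrong to assume that every register can supply the earlier months: the article shows this for the EHR only. The recommendation is worth making because it costs little and serves a stated hypothesis.

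**What to change.** Where permits and existing consent allow, extend the EHR extraction to the 12 months before randomisation. Do the same for the Social Insurance Institution extraction if its earlier months are available. In the hip fracture group, use the 12 months ending the day before the index fracture, so that the fracture admission is not counted as prior use.

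Add a month-0 entry to the service use and costs row of Table 1. Before the outcome data are analysed, pre-specify log(prior-year cost + 1) as a covariate in the cost model, and prior-year hospital days in the service-use model, within the log-link gamma models already planned.

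If the earlier months cannot be released, pre-specify as covariates the month-0 service, medication and function items already collected.

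The cost is a permit and consent check and a somewhat larger data request. No visit or patient contact is added. Allocation cannot affect pre-randomisation records, so late extraction introduces no bias.
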